#### Secondary outcomes

1. National Institute of Health stroke scale (NIHSS). The NIHSS is used to evaluate the severity of stroke patients. Changes in NIHSS scores after one week in acute ischemic stroke patients with different ventilation modes. NIHSS scores range from 0–42, with higher scores indicating more severe neurological damage. 2. Barthel index. The Barthel index is used to assess the ability of stroke patients to live independently. This study assesses whether the quality of life of patients with acute ischemic stroke improves at one month and three months. 3. Sleep apnea symptoms. To assess changes in sleep apnea symptoms in patients with acute ischemic stroke. After one week of treatment with different ventilation modalities, polysomnography will be performed again to assess whether sleep has improved in stroke patients by calculating the magnitude of the AHI value. The minimum value of the AHI is 0, and there is no maximum value. A higher AHI value indicates more severe sleep apnea symptoms; 4. Time of hospitalization; 5. Cost of hospitalization; 6. Neurological recovery (mRS).

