**Discussion:**

This study analyses different ventilation modalities for early interventions in patients with sleep apnea after AIS. We will investigate whether nCPAP and HFNC reduce early mortality and endotracheal intubation rates and improve distant neurological recovery in patients.

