### Exclusion criteria

1. Pre-existing obstructive sleep apnea; 2. Suspected sleep disorders other than sleep apnea (e.g., episodic sleeping sickness); 3. Respiratory distress requiring mechanical ventilation; 4. Oxygen-dependent chronic obstructive pulmonary disease; 5. Pregnancy; 6. Intracranial haemorrhage; 7. Inability to use a nasal mask or mask (e.g., facial trauma); 8. Patients who died within 24 h of admission; 9. History of other neurological disorders such as Parkinson's, neuro infection, and neuromuscular disease patients; 10. Hospice care or comfort measures only; 11. Inability to provide informed consent; 12. Inability to provide valid information; 13. Suicidal ideation.

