### Study outcomes

#### Primary outcomes

1. 28-day mortality rate; 2. Tracheal intubation rate (Rate of tracheal intubation in each group after one week using different ventilation methods); 3. Pulmonary infection rate (Rate of pulmonary infections in each group after one week using different ventilation methods).

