### Statistical analysis

The final data analysis will be done by statisticians uninvolved in the clinical trial and kept blind. The three data sets will be done by one-way ANOVA (normally distributed data) or Kruskal–Wallis statistics (non-parametric data). Categorical variables are done via chi-square tests. In addition, logistic regression and propensity score matching (PSM) will be used to adjust for the effect of multivariate risk factors on early clinical outcomes. Survival analysis will be performed using the Kaplan–Meier method. All statistical analyses will be performed by SPSS 22.0 (IBM SPSS Statistics 22.0, SPSS Inc., Chicago, IL) and R language (version 4.1.3, www.R-project.org/). Statistical significance is expressed as *p* < 0.05.

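### Time of hospitalization carries no provision for in-hospital death, and the only tests named for continuous data would read an early death as a short stay

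*Protocol article*

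**What the plan says.** Under Secondary outcomes, the protocol article lists "4. Time of hospitalization; 5. Cost of hospitalization". It gives no start, end or unit for the stay and no rule for patients who die in hospital.

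Under Statistical analysis, the group comparison for continuous data is "one-way ANOVA (normally distributed data) or Kruskal–Wallis statistics (non-parametric data"). The same section adds that "Survival analysis will be performed using the Kaplan–Meier method", without naming the outcome to which this applies. No competing-risk method is named.

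The first primary outcome is the "28-day mortality rate", and the abstract says the trial will examine "whether nCPAP and HFNC reduce early mortality and endotracheal intubation rates". The exclusion criteria include "8. Patients who died within 24 h of admission"; later in-hospital deaths remain in the trial. The Missing data plan sets complete-case analysis or multiple imputation according to how many participants are missing, and does not mention death.

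**The concern.** Death ends a hospital stay. A patient who dies on day 4 has a complete, observed stay of 4 days. The missing-data rule does not reach it, because nothing is missing. ANOVA and Kruskal–Wallis on days in hospital place that patient on the favourable side of one discharged alive on day 14.

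This matters when mortality differs between arms, which is what the trial hopes to show. If a device lowers early mortality, its arm keeps more patients in hospital for longer. That can cancel a real gain in discharge speed, or make stay look longer when discharge speed is the same. A device that raised early mortality would gain a shorter stay, and probably a cheaper one. Kaplan–Meier does not settle the matter. Counting death as the end of stay repeats the problem, and censoring deaths treats the dead as still due for discharge.

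**Working it through.** **Inputs from the article.** 150 patients randomised 1:1:1, so 150/3 = 50 per arm; significance at p < 0.05; ANOVA or Kruskal–Wallis across three groups. The article gives no expected mortality and no stay distribution, so there is no planned figure to reproduce.

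**Assumptions.** Time to live discharge is lognormal with median 14 days and log-SD 0.5. In-hospital deaths fall uniformly over days 1–11. Mortality is varied and written as standard/HFNC/nCPAP. Each scenario has 2000 replicates.

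**Step 1: direction and size of the shift.** With mortality m, mean discharge time S and mean death day D, the mean observed stay is (1 − m)S + mD. Two arms with the same discharge speed therefore differ by (difference in m) × (S − D).

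- S = 14 × exp(0.5²/2) = 15.86 days; D = (1 + 11)/2 = 6 days; S − D = 9.86.
- Mortality 20% v 10%: 0.10 × 9.86 = 0.99 days longer in the arm with fewer deaths.
- Mortality 10% v 5%: 0.05 × 9.86 = 0.49 days.
- Deaths over days 1–28: D = 14.5, S − D = 1.36, so 20% v 10% shifts the mean by only 0.14 days.

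A simulation with a different death-time model (mean about 5 days) gives 13.6 v 14.8 days at 20% v 10%, a shift of about 1.1 days. That agrees with 0.10 × (15.86 − 5) = 1.09. Moving the mean death time between 8 and 3 days gives shifts of 0.9 to 1.3 days.

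**Step 2: Kruskal–Wallis on days to death or discharge, deaths on days 1–11.** The second column has equal discharge speed in all arms. The last two have true medians of 14/11.5/10.5 days.

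| Mortality | Rejection, equal speed | Power, all days as observed | Power, survivors only |
|---|---|---|---|
| 6/3/3% | 5% | 57% | 70% |
| 10/5/5% | about 6% (7% in one run) | 49% | 68% |
| 15/8/5% | 9% | 34% | 66% |
| 20/10/10% | 11% | 27% | 63% |
| 20/10/5% | 14% | 20% | 65% |
| 25/10/10% | 18% | 18% | 61% |

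Repeat runs of the last four rows give 8–18%, 16–32% and 60–65%. With mortality of 10% in every arm, rejection at equal speed is 5.0% and power is 56%, so the false-positive inflation comes from the mortality difference. The survivors-only column is a yardstick for the information on discharge speed, not a proposed analysis, since it selects on an event after randomisation.

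**Step 3: sensitivity to death timing.** With deaths uniform over days 1–28, and the death day taken as drawn, rejection at equal speed is 4.6–5.6% in the last four scenarios and little power is lost. This fits the small shift in Step 1.

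**Step 4: worst rank as a remedy.** Giving in-hospital deaths the longest stay raises rejection in the unequal-speed scenarios to 82%, 77%, 90% and 88% (last four rows). At equal discharge speed, however, it rejects in 11%, 13%, 21% and 24%, at least as often as days as observed. It picks up the mortality difference itself, so its power is not comparable with the other columns.

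**The case against.** A reader might infer that the plan prescribes an analysis of raw days and scores an early death as a short stay. The article does not say so. The tests are tied to no outcome, Kaplan–Meier is named without one, and a time-to-discharge analysis is not ruled out. A rule for deaths could sit in the full protocol or SAP, which are not shown. Patients who deteriorate may be withdrawn, so some may never enter as short stays.

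The effect may also be slight. Eligibility (NIHSS 2–20, GCS of at least 9, no need for mechanical ventilation, no comfort-only care, no death within 24 h) removes many high-risk patients, and at low mortality false rejection is close to nominal. Stay is listed beside cost, which fits a resource-use reading for which bed-days including deaths are legitimate. Mortality will be reported in any case.

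Most of this stands, and it limits the point to what the named tests would do if applied as written. It does not remove it. ANOVA or Kruskal–Wallis is the only group comparison given for continuous data, and nothing stated provides for death. Dropping the stays of withdrawn patients would replace one problem with a selection made after randomisation. A resource-use reading is sound only if a shorter stay is not then presented as benefit.

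**Conclusion.** The point holds as a minor one. The stated method, applied to days in hospital, reads early in-hospital death as a favourable result in a trial that expects mortality to differ. The direction follows from arithmetic; the size does not follow from the article and rests on assumed mortality, stay and death timing.

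With early deaths, false positives are nearly absent up to 10/5/5% mortality and become material from 15/8/5% upwards. Loss of power appears sooner, at about 19 points for 10/5/5% (68 − 49). With deaths spread over 28 days, both largely vanish. The documents do not support saying that the trial will report a spurious longer stay, nor that worst-rank scoring would recover 77–90% power for discharge speed. The outcome is secondary, and no primary comparison is affected.

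**What to change.** In Secondary outcomes and Statistical analysis, define the outcome as time from randomisation to discharge alive over a fixed window, for example 28 days or 3 months. Treat in-hospital death as a competing event, compare cumulative incidence of live discharge between arms by Gray's test, and show deaths by arm beside it. Report raw bed-days and cost as resource use only, and state that a shorter stay or lower cost will not be read as benefit on its own. Worst-rank scoring should be at most a sensitivity analysis.

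The cost is a change of wording, and R is already named. The analysis needs dates of randomisation, discharge and in-hospital death. The article's list of trial data does not name these, so their collection should be confirmed. The drawback is that cumulative incidence of live discharge reflects survival as well as discharge speed, so it must be read with mortality; worst rank mixes the two even more.

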### Quality control

Differences in scores may result from the clinical experience of the doctors. Therefore, each patient's assessment is administered by the same doctor to ensure accuracy and consistency of scoring each time. Additionally, the performer is trained several times prior to conducting the assessment.

### Data collection and follow-up

All participants in the clinical trial are assessed at baseline, and a specialist team member records information. Trial data includes baseline information (age, sex, height, weight, heart rate, blood pressure), previous medical history (history of surgery, family history, history of smoking and alcohol consumption), laboratory findings, imaging findings (brain MRI or CT), polysomnography findings, NIHSS score, mRS, Barthel Index, acute physiology and chronic health evaluation (APACHE) II score, GCS score, etc. Telephone follow-up is conducted one week, one month and three months after the participants are discharged from the hospital according to the plan developed for the study to assess the participants' neurological recovery and prognosis.

### Data management

All data from the clinical study will be entered directly into the computer via EpiData V.3.1 (EpiData Association, Odense, Denmark). The study team will enter the data, and the data's accuracy will be verified by the study's principal investigator (PI). All data is protected and stored securely at the study site. Researchers can only access information by entering the correct username and password. The participants' privacy is fully protected in this study, and all participants will not be identified by name. Post-discharge follow-up is achieved through each participant's unique number and telephone number at the time of admission. The PI of the study will have access to the final study data set.

### Data and safety monitoring

An independent data monitoring committee includes neurologists, respiratory and critical care physicians, emergency medicine physicians, statisticians and data management staff. The committee will meet twice during the year, and its main task is to monitor and review the data.

### Statistical analysis

The final data analysis will be done by statisticians uninvolved in the clinical trial and kept blind. The three data sets will be done by one-way ANOVA (normally distributed data) or Kruskal–Wallis statistics (non-parametric data). Categorical variables are done via chi-square tests. In addition, logistic regression and propensity score matching (PSM) will be used to adjust for the effect of multivariate risk factors on early clinical outcomes. Survival analysis will be performed using the Kaplan–Meier method. All statistical analyses will be performed by SPSS 22.0 (IBM SPSS Statistics 22.0, SPSS Inc., Chicago, IL) and R language (version 4.1.3, www.R-project.org/). Statistical significance is expressed as *p* < 0.05.

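### Propensity score matching is planned beside logistic regression in a randomised trial, and the continuous secondary outcomes have no baseline-adjusted model although their baselines are collected

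*Protocol article*

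**What the plan says.** All of the methods stand in the Statistical analysis section of the protocol article.

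- Continuous data are compared across the three arms by "one-way ANOVA (normally distributed data) or Kruskal–Wallis statistics (non-parametric data").
- For binary and other categorical data: "Categorical variables are done via chi-square tests".
- As an addition to these tests, "logistic regression and propensity score matching (PSM) will be used to adjust for the effect of multivariate risk factors on early clinical outcomes".

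No baseline-adjusted model is named for a continuous outcome.

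Under Data collection and follow-up, "All participants in the clinical trial are assessed at baseline", and the list of trial data includes "polysomnography findings, NIHSS score, mRS, Barthel Index". The AHI comes from the polysomnography.

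Under Secondary outcomes, the NIHSS is defined as a change: "Changes in NIHSS scores after one week in acute ischemic stroke patients with different ventilation modes". For sleep apnea, "polysomnography will be performed again to assess whether sleep has improved in stroke patients by calculating the magnitude of the AHI value", with the aim of assessing change, but whether the analysed quantity is the one-week value or its difference from baseline is not fixed. The Barthel index is assessed for improvement at one and three months.

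**The concern.** Propensity score matching is a tool for non-randomised comparisons, where the chance of receiving a treatment is unknown and depends on prognosis. Here that chance is one third by design. A fitted score therefore describes only chance imbalance.

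Matching on it has three drawbacks:

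- With a caliper, patients without a close counterpart are removed, and the estimate then refers to a subset chosen by the data, not to the randomised population.
- With three arms, matching is either done pairwise, with a possibly different subset for each contrast, or three-way.
- The binary primary outcomes acquire a second adjusted result beside the logistic regression, and its value depends on matching choices that regression does not need.

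For NIHSS, AHI and Barthel the issue is efficiency. Eligibility spans NIHSS 2 to 20, and the randomisation is blocked with no stratification described. The analysis is therefore the only stated place where baseline severity could be taken into account. With about 50 patients per arm, precision that is free to obtain should not be given up.

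**Working it through.** **Inputs from the protocol article.** Three arms, 1:1:1, 150 patients, so 150/3 = 50 per arm. With the stated 10% loss, 0.9 × 50 = 45 per arm. The plan attaches no figure of its own to matching or to baseline adjustment, so there is none to reproduce.

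**Inputs that are assumptions.** The article gives no matching ratio, caliper or covariate number. Assumed: greedy 1:1 nearest-neighbour matching without replacement, a caliper of 0.2 SD of the logit of the score, and 3 to 10 independent covariates. It also gives no SD or baseline-to-follow-up correlation r. Assumed: r from 0.3 to 0.7, with equal SD at both times.

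**1. What matching discards.** Two randomised arms with no true imbalance were simulated, 400 runs per setting. Mean share of patients kept:

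| Covariates | 45 per arm | 50 per arm |
|---|---|---|
| 3 | 74% | 75% |
| 5 | 72% | 74% |
| 8 | 69% | 71% |
| 10 | 67% | 69% |

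The loss is thus about 25% (50 per arm, 3 covariates) to 33% (45 per arm, 10 covariates) per pairwise comparison. At 45 per arm, 30 to 33 remain. If the arms are equal and there is no caliper, every patient is paired. The two matched groups are then the original arms, and balance is what it was before.

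**2. What that costs in precision.** This depends on whether the covariates predict the outcome. The SD of the estimated difference was compared with that of the unadjusted estimate (simulated continuous outcome, 50 per arm, 4 to 10 covariates, same caliper):

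- Covariates unrelated to outcome: about 1.2 times after matching. The simple calculation agrees: √(50/36.3) = 1.17 at 6 covariates.
- Covariates explaining 30 to 50% of the outcome variance (assumed): about 0.9 to 1.05 times after matching, against about 0.7 to 0.9 times for regression on all patients.

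Matching ranges from a clear loss to a small gain against the unadjusted test, but regression on the same covariates was more precise in every setting.

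**3. Baseline adjustment of continuous outcomes.** Relative to the variance of a follow-up-only comparison (set to 1):

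- change score: 2(1 − r)
- ANCOVA: 1 − r²
- ANCOVA against change score: (1 − r²) / [2(1 − r)] = (1 + r)/2

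| r (assumed) | Change score | ANCOVA | ANCOVA / change | 45 per arm is worth, 45/(1 − r²) |
|---|---|---|---|---|
| 0.3 | 1.40 | 0.91 | 0.65 | 49 |
| 0.5 | 1.00 | 0.75 | 0.75 | 60 |
| 0.7 | 0.60 | 0.51 | 0.85 | 88 |

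For an assumed pairwise difference of 0.5 SD at 45 per arm (two-sided 5%), power is 66% for follow-up only. For r = 0.3, 0.5 and 0.7 it is 52%, 66% and 87% for the change score, and 70%, 78% and 91% for ANCOVA.

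**The case against.** The strongest reply is that little depends on matching. Logistic regression is named first in the same sentence and uses every patient with data. Both adjusted methods are additions to full-sample tests. Matching is not made the main analysis, and no primary comparison is invalidated. All of this stands.

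It also rules out several stronger readings that a reader might infer:

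- *That adjustment rests on matching alone, or that the matched subset replaces the randomised set.* The text says neither.
- *That baseline values are ignored throughout.* This is untrue for the NIHSS, which is analysed as a change. A change-score comparison is valid under randomisation. For AHI and Barthel the outcome wording speaks of change or improvement, so it is not established that baseline goes unused. What is missing is a model that uses it efficiently.
- *That precision is lost twice.* Matching concerns early clinical outcomes, of which the primary ones are binary. The ANCOVA point concerns continuous secondary outcomes. No single outcome is shown to suffer both.
- *That confidence intervals widen by a fixed 17%.* That figure needs the assumed caliper and covariates unrelated to outcome.
- *That open covariate lists are a defect.* They may stand in an analysis plan that is not shown.

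The ANCOVA formulas are for linear models, and the article provides Kruskal–Wallis for non-normal data. The size of the gain is therefore a guide only. The reply does not supply a reason to keep matching: without a caliper it changes nothing, and with one it drops patients whom the neighbouring regression keeps.

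**Conclusion.** The point holds as a choice of method that should be improved, not as an error that invalidates the trial. The article itself names the methods, so this is not a matter of detail left to another document.

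Matching can remove randomised patients, about 25 to 33% per pairwise comparison under the assumed caliper and covariate numbers, and has no evident advantage over regression on all patients. For NIHSS, AHI and Barthel, ANCOVA is in large samples never less efficient than the follow-up or change-score comparison. At an assumed r of 0.5 to 0.7 its variance is 0.75 to 0.85 of a change-score analysis and 0.75 to 0.51 of a follow-up-only analysis. The direction of both conclusions does not depend on the assumed values; the sizes do.

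**What to change.** 1. Delete propensity score matching from the Statistical analysis section.
2. For binary outcomes, keep logistic regression as the single adjusted analysis, on all randomised patients, with arm and a few pre-named baseline covariates (for example age and baseline NIHSS). State that a penalised fit, such as Firth's, is used if events are few.
3. For one-week NIHSS and AHI, and for Barthel at one and three months, replace one-way ANOVA by ANCOVA: the follow-up value on arm plus the same measure at baseline, rank-based or transformed if skewed. Take the baseline AHI from a recording made before the allocated treatment starts.

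The cost is analysis wording only. The article already lists age, NIHSS, Barthel and polysomnography among the baseline data, so no new data, visits or patients are needed.

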### Missing data plan

During the clinical trial, if data are missing, we will record the reason for the absence and the amount of data. During follow-up, if < 10% of participants are missing, we will use the complete case method. If ≥ 10% of participants are missing, and we will use the multiple imputation method to impute missing values.

### Adverse events

During the trial, a senior practitioner will assess any adverse events experienced by participants, and the participant's family will be informed promptly. Participants will be withdrawn from the trial in a timely manner if their condition worsens or they are unfit to continue participating.

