### Withdraw criteria

1. Unable to tolerate the clinical trial and requesting an early withdrawal. 2. Patient is unsuitable for further trials due to deterioration. 3. Poor compliance with the follow-up plan.

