### Sample size

The sample size is calculated using the Contingency Table (Chi-Square Tests) in the PASS 15.0 software. A literature review showed that nCPAP was approximately 65% effective for neurological recovery in stroke patients and 55% effective for HFNC, compared to 40% in the standard oxygen therapy group [14, 15]. In this study, the test level α = 0.05 and the test efficacy 1-β = 0.9. The final sample size is expected to be 150 cases, considering a 10% loss to follow-up rate, including the possibility of deterioration after admission and loss to follow-up after discharge.

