### Control group

In the trial, participants in the control group are treated with either conventional nasal cannula oxygen therapy or mask oxygen therapy. Treatment and care remained the same, except that the oxygen therapy is administered differently from the intervention groups. Participants will be monitored during their stay in the hospital and withdrawn from the clinical trial if necessary.

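### Patients are withdrawn from the trial when they worsen and counted as lost, although worsening leads to all three primary outcomes; neither branch of the missing-data rule repairs this

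*Protocol article*

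**What the plan says.** All references are to the protocol article.

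- **Adverse events:** "Participants will be withdrawn from the trial in a timely manner if their condition worsens or they are unfit to continue participating". The patient leaves the trial, not only the assigned ventilation.
- **Withdraw criteria, item 2:** "Patient is unsuitable for further trials due to deterioration". Items 1 and 3 read "Unable to tolerate the clinical trial and requesting an early withdrawal" and "Poor compliance with the follow-up plan".
- **Control group:** participants are monitored in hospital and "withdrawn from the clinical trial if necessary". The Intervention groups section has a parallel clause on termination.
- **Sample size:** 150 patients, allowing 10% loss to follow-up, "including the possibility of deterioration after admission and loss to follow-up after discharge".
- **Missing data plan:** if fewer than 10% "of participants are missing, we will use the complete case method"; at 10% or more, multiple imputation. The percentage is of participants, with no mention of arm.
- **Primary outcomes:** 28-day mortality, intubation at one week and pulmonary infection at one week.
- **Randomisation and blinding:** 1:1:1 allocation; treating staff and patients know the arm.
- **Exclusion criteria, item 8:** "Patients who died within 24" hours of admission.

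**The concern.** Clinical worsening is the usual route to death, intubation and pulmonary infection. A rule that removes a patient from the trial on worsening therefore acts just before the primary event, or at the same moment. The Sample size section shows that the planners expect such patients to count as lost.

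If their outcomes are not collected, event rates are too low in every arm. If removal is more frequent in one arm, that arm looks better than it is. The trial is open-label, so whoever judges that a patient has worsened knows the arm, and nothing in the stated rules keeps removal equal across arms. The comparison is then no longer between the groups as randomised, and this affects all three primary outcomes.

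**Working it through.** **1. The sections side by side.** Adverse events and Withdraw criteria item 2 make worsening a reason to leave the trial. Sample size puts deterioration under loss to follow-up. Primary outcomes names three events that worsening precedes. No section says that outcomes are still collected after withdrawal. The loss of these outcomes is an inference, but the Sample size wording makes it the natural one.

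**2. What the Missing data plan does with the lost patients.** 10% of 150 is 15.
- 14 or fewer missing (14/150 = 9.3%): complete case. The patient leaves both numerator and denominator.
- 15 or more missing: multiple imputation. The planned 10% loss itself falls in this branch.
- The count runs over all arms. As an extreme case, all 14 could come from one arm (14/50 = 28%) and complete case would still apply.

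Standard multiple imputation assumes missing at random given the observed data. That does not hold when patients are missing because they worsened, so neither branch repairs the problem.

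**3. Effect on the observed rate.** Let p be the true event rate and r the fraction of events lost through prior withdrawal. Under complete case the observed rate is p(1 − r)/(1 − pr). The documents give neither p nor r; both are assumed.

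| True p | r = 25% | r = 50% |
|---|---|---|
| 10% | 0.075/0.975 = 7.7% | 0.05/0.95 = 5.3% |
| 20% | 0.15/0.95 = 15.8% | 0.10/0.90 = 11.1% |
| 30% | 0.225/0.925 = 24.3% | 0.15/0.85 = 17.6% |

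Example with p = 20% in all three arms of 50 (10 events each) and 0%, 25% and 50% of events lost: 0 + 2.5 + 5 = 7.5 patients go missing on average (5% of 150, so complete case applies if nothing else is missing). The arms show 20.0%, 15.8% and 11.1%, although they do not differ.

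**4. Effect on the false-positive rate.** Simulation with 50 per arm, equal true rates, Pearson chi-square at 0.05 and complete case:

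| True p | Two arms, 0% vs 25% lost | Two arms, 0% vs 50% lost | Three arms, 0/0/50% lost |
|---|---|---|---|
| 10% | about 7% | about 13% | about 11% |
| 20% | about 8% | about 22% | about 19% |
| 30% | about 10% | about 28% | about 26% |

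At p = 20%, 25% versus 50% lost gives about 10%, and three arms with 0/0/25% lost give about 8%. Equal loss of 50% in both arms gives about 5%: the test keeps its level, but both rates are understated.

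**The case against.** Five points can be made for the plan.

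- **No section says that data collection stops at withdrawal or that earlier events are discarded.** An intubation or infection that is itself the worsening may already be recorded. Definitions of analysis sets are often left to a full protocol or SAP that is not shown. This stands in part: lost outcomes are inferred, and a missing analysis-set definition is not the finding. But an SAP cannot analyse outcomes that were never collected, and the article's own words class deterioration as loss.
- **The plan does provide multiple imputation.** True, and at the planned 10% loss that branch applies. A reader might infer that withdrawn patients are always dropped; the text does not support that. The objection fails only because imputation under missing at random does not fit this mechanism.
- **Only deterioration is clearly tied to outcome.** A reader might infer that patients who cannot tolerate the device, or use it poorly, are also removed. The text does not say so. Item 1 concerns intolerance of the trial together with the patient's own request to leave, and item 3 concerns compliance with follow-up. Neither names the device.
- **Withdrawal rules cover every arm.** True, and the Control group section says so for controls. If loss is equal, the false-positive rate stays near 5%. Equal loss is not assured in an open-label trial.
- **Kaplan–Meier analysis is planned** and would keep a withdrawn patient at risk until censoring. But censoring at worsening is informative, so the bias remains.

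**Conclusion.** The concern holds for withdrawal on deterioration. The plan's stated rules remove patients on the path to the primary outcomes and count them as lost, and the stated missing-data rule handles that loss inadequately in both branches. It should be corrected before analysis, because every primary comparison is exposed.

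The size is uncertain. Over assumed event rates of 10% to 30%, the two-arm false-positive rate runs from near 5% with equal loss, through about 7% to 10% when a quarter of one arm's events are lost, to about 13% to 28% when half are lost. The last range is an unfavourable scenario, not an expectation. All these figures assume that outcomes after withdrawal are not collected and that complete case applies; other missing data could move the trial into the imputation branch.

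A reader might also infer that exclusion criterion 8 deletes deaths after randomisation. That would follow only if patients can be randomised within 24 hours of admission, and the article gives no such timing. It is a secondary, conditional point.

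**What to change.** 1. Separate stopping the assigned ventilation from leaving the study. The clinical decision to stop is unchanged. For every randomised patient, unless consent is withdrawn, collect 28-day vital status, one-week intubation, one-week pulmonary infection and the planned follow-up outcomes, from hospital records and the telephone calls already scheduled.
2. Analyse all randomised patients in their allocated arm.
3. For outcomes still missing, do not rely on the overall 10% switch. Add a sensitivity analysis for data not missing at random, for example worst case by arm. Extending multiple imputation to any level of missingness would not be enough by itself.
4. Reconcile Withdraw criteria, Sample size, Control group, Intervention groups, Missing data plan and Adverse events, so that each says whether it means stopping the ventilation or ending follow-up.
5. If randomisation can occur within 24 hours of admission, apply exclusion criterion 8 only before randomisation and count every later death.

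The cost is amendment wording, some extra record checking and a modest amount of analysis. No new visits are needed.
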